### Procedure for informed consent

Schools directors/heads will be approached and a letter will also be sent inviting them to participate. All the teachers in the consenting schools who are willing to participate will be recruited for the study. Teachers will be invited to attend an informal meeting/workshop by the PI, who will provide an overall view of the study. A description of the WHO-EMRO Manual including its rationale, the format of the interventions proposed and anticipated potential benefit to the target population will be provided. The workshop will also help to gain key stakeholder support for the project and augment understanding of local schools mental health strategies. Teachers will also have the opportunity to discuss and clarify any aspect of the project. Written informed consent will be obtained from teachers before participating in the RCT. To ensure anonymity, participating teachers will be requested not to provide any identifying information on the test questionnaire, rather to anonymously identify information like mother’s first name. This information will be used to link pre-and post-training responses. All the parents of eligible students (11–16 years) in the participating schools will receive an information letter regarding the teacher training, study project and data collection of their children. and a written informed consent form. Assent from the students will be required prior to answering the questionnaire.

### Randomization

Participants will be randomly allocated to the intervention group (receiving school mental health intervention during the study) or the waitlist control group (no training) using computer-generated random numbers. Randomization will be done by a statistician not directly linked to the study using the teachers list provided by the schools. The intervention delivery team will not be involved in the randomization procedure.

#### Blinding

It is not possible for study participants to be blind to intervention status. However, other staff members assisting with data collection from teachers and students, data input and the statistical support persons helping with analysis will be blind to the intervention status (Fig. 2).

**Fig. 2 Fig2:**
[figure not shown]
Trial schema

### Outcome measures

Table 2 shows the outcomes to be collected at each time point.

**Table 2 Tab2:** Outcomes to be collected by time point

	Baseline	Immediate post intervention	3 months’ follow up
Teacher	Mental health literacy: Self-administered Knowledge, Skills and Attitudes Questionnaire^a^ Teachers’ Sense of Self Efficacy Scale (TSES): short form	Mental health literacy: Self-administered Knowledge, Skills and Attitudes Questionnaire^a^ Teachers’ Sense of Self Efficacy Scale (TSES): short form	Mental health literacy: Self-administered Knowledge, Skills and Attitudes Questionnaire^a^ Teachers’ Sense of Self Efficacy Scale (TSES): short form
Students	Strengths and Difficulties Questionnaire (SDQ) 11–16	–	Strengths and Difficulties Questionnaire (SDQ) 11–16
Schools	Psychosocial Profile Questionnaire	–	Psychosocial Profile Questionnaire

^a^Primary outcome

#### Primary outcome: assessment of mental health literacy of teachers, using a self-administered questionnaire

The primary outcome measures for the trial is teachers’ mental health literacy immediately post intervention. Mental health literacy refers to a person’s knowledge and beliefs about mental disorders, which in turn increases their ability to recognize, manage, or prevent the development or exacerbation of mental health problems [16]. It has various elements including: (1) enhancing the capacity to obtain and maintain good mental health; (2) enhancing understanding of mental disorders and their treatments; (3) decreasing stigma related to mental illness; and (4) enhancing help-seeking efficacy [17].

It will be assessed by using previously applied (during WHO training of Master Trainers) pre and post tests in both groups, that were reviewed for cultural appropriateness by Pakistani mental health experts. The initial section of questionnaire has 30 multiple choice questions. Possible responses are ‘true’, ‘false’ and ‘I don’t know’. The next section has six stories with five questions each of possible interventions to be considered by school teachers. Each question has a ‘yes’, ‘no’ format. Participants will be instructed to choose only one option per question and will be encouraged to mark ‘I don’t know’ rather than guessing. A total score out of 60 maximum will be calculated.

Demographic information, length of teaching experience, information about classes they teach (primary, secondary, both), and previous training on similar topics will also be collected from all teachers in both groups.

#### Secondary outcome measures

##### Teachers

*Teachers’ Sense of Self Efficacy Scale (TSES): short form*

The TSES measures teachers’ assessment of their self-efficacy for teaching tasks as well as their other responsibilities [18]. There are 12 statements and each statement is rated on 9-point Likert scale. Permission was obtained from the authors of the scale. Teachers’ efficacy in student engagement and classroom management subscales will be used in the study, as they relate to the content of the intervention.

##### Students

*Strengths and Difficulties Questionnaire (SDQ)*

The Strengths and Difficulties Questionnaire (SDQ), a universally validated tool, will be used to screen students for behavioral and emotional problems. The SDQ has various versions; parents, teachers and self-administered for students. We will be using, self- reported SDQ (11–16 years). The SDQ measures 25 attributes, which are grouped in subscales of five items each, generating scores for conduct, hyperactivity, emotional, peer problems and prosocial behavior. Statements are rated on a 3-point Likert scale:0 (not true), 1 (somewhat true) and 2 (certainly true). All scales excluding the last are added to generate a total difficulties score (0–40). Total difficulties and categories scores can be coded into normal, borderline and abnormal categories [19, 20].

##### Schools

*School Psychosocial Profile Questionnaire*

The WHO Psychosocial Profile Questionnaire has grouped various school characteristics in seven quality areas. An average score of each quality area is calculated.

### Statistical analysis

Data will be analyzed using SPSS 20. A description of baseline characteristics of schools and of individuals who participate in the two intervention arms will be compiled using descriptive statistics such as mean and standard deviation, frequency and percentages. Aggregates of the mean item score will be created for each scale at three timelines (baseline T0, immediately following intervention T1, and 3 months following intervention T2). Paired samples’ *t* tests will be used to examine differences in knowledge and attitudes scores and self-efficacy between participants at T0, T1 and T2. Differences in mean scores between the study and control groups will be evaluated using an independent samples’ *t* test. Intention-to-treat analysis will be used for data analysis. Student outcome measures for schools and the psychosocial environment will be compared at baseline and follow-up using the *t* test. Statistical significance will be fixed at a level of *P* < .05. Data on screening, refusals and dropouts will be reported as per Consolidated Standards of Reporting trials (CONSORT) guidelines for participant flow through the trial.

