### Aims and objectives of the study

This pilot RCT seeks to demonstrate the effectiveness of a teacher training programme based on the WHO-EMRO Manual of School Mental Health in improving teacher’s mental health literacy as compared to a waitlist control group. The secondary objective is to evaluate the effect of the WHO-EMRO School Mental Health Manual-based intervention in improving self-efficacy among school teachers. The study will also determine if mental health training of teachers may lead to an indirect improvement in a students’ outcome measure (emotional and behavioral difficulties) and the school psychosocial environment.

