### Participants and sample size

All the teachers in the participating schools of grades 1–10 of both genders will be approached. Exclusion criteria included lack of informed consent, teachers who are leaving/not planning to be in the school in 3 months’ time, and teachers who have not been involved in active teaching in last 6 months. Students of 11–16-years old studying in the participating schools whose parents will give informed consent will also be screened.

A sample size of 220 teachers (110 teachers each in the intervention and control groups) is estimated using 90% confidence interval, 5% absolute precision with expected percentage of improvement on mental health literacy in the intervention group as 10% and the control group as 1% [14].

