### Study design

The study is a two-arm RCT. We expect to include five to six schools to obtain the required sample size. Schools will be sent a letter inviting them to participate. All the teachers in the consenting schools, who are willing to participate, will be recruited for the study. Participants will be randomly allocated to the intervention group (receiving the school mental health intervention during the study) or the waitlist control group (teachers who will not receive any training during the study period) using computer-generated random numbers. In order to evaluate the effectiveness of training, a pre- and post-study design will be used (see the Standard Protocol Items: Recommendations for Interventional Trials (SPIRIT) Diagram in Fig. 1). Participants’ mental health literacy and self-efficacy will be evaluated using questionnaires pre and post training and at 3 months’ follow-up. Students (11–16 years old) taught by these teachers and the school psychosocial environment will also be screened at baseline and 3 months after the intervention using the self-reported SDQ. The study follows the Consolidated Standards of Reporting Trials (CONSORT) Guidelines for the design and implementation of RCTs [15].

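### Paired pre-post tests and a between-arm t test are both planned at P < .05, and the plan does not say which one decides effectiveness

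*Protocol article*

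**What the plan says.** All references are to the protocol article.

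- **Aims and objectives of the study** sets a comparative objective: effectiveness "in improving teacher’s mental health literacy as compared to a waitlist control group".
- **Study design**, after describing random allocation to two arms, adds: "In order to evaluate the effectiveness of training, a pre- and post-study design will be used".
- **Primary outcome** fixes one outcome and one time: "The primary outcome measures for the trial is teachers’ mental health literacy immediately post intervention". On the score it says: "A total score out of 60 maximum will be calculated".
- **Table 2** attaches the primary-outcome footnote to the literacy questionnaire in all three columns: baseline, immediately post intervention and 3 months.
- **Statistical analysis** first forms the scores: "Aggregates of the mean item score will be created for each scale at three timelines". It then states that paired t "tests will be used to examine differences in knowledge and attitudes scores and self-efficacy between participants at T0, T1 and T2". The next sentence reads "Differences in mean scores between the study and control groups will be evaluated using an independent samples" t test. Intention to treat and a single significance level of P < .05 follow, with no ranking of the tests.

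**The concern.** A paired t test measures change within the same people. It does not compare training with the waitlist, so it cannot answer the stated objective. The sentence that plans it also describes it wrongly, as a comparison among participants, and does not say whether it is run in each arm or in both arms pooled.

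The paired tests come first, share the significance level of everything else and are given no descriptive or supporting role. The between-arm test is the one that matches the objective, yet its sentence names no outcome or time point. The Study design sentence on effectiveness points towards pre-post change, and Table 2 blurs the time point that the Primary outcome section fixes.

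Both arms complete the same questionnaire three times, so scores may rise simply because teachers have seen the questions before. A reader following the plan as written could report a significant pre-post rise in trained teachers as evidence that training works. The Dissemination section makes this consequential: a finding of effectiveness is to go to policy-makers with a view to mandatory teacher training.

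**Working it through.** **1. The plan's own figure.** Participants and sample size gives "A sample size of 220 teachers (110 teachers each in the intervention and control groups"), based on a 90% confidence interval, 5% absolute precision, and improvement of 10% against 1%. The precision formula for a difference of two proportions is

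n per arm = z² × [p₁(1 − p₁) + p₂(1 − p₂)] / d²

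= 1.645² × (0.10 × 0.90 + 0.01 × 0.99) / 0.05² = 108.1, rounded up to 109.

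This reproduces the stated 110. The sample size therefore rests on a contrast between arms, not on change within an arm.

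**2. Retest gain alone.** Inputs:

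- From the document: 110 per arm, and level 0.05. The document does not state sidedness; two-sided is assumed.
- Assumed, because the document gives neither: a retest gain g of 0.1, 0.2 or 0.3 SD, equal in both arms, and a pre-post correlation ρ of 0.5 or 0.7.
- Also assumed: no training effect, normal scores, no dropout and no clustering.

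The SD of change, in units of the score SD, is √[2(1 − ρ)]: 1.000 at ρ = 0.5 and 0.775 at ρ = 0.7. The approximate chance that the trained-arm paired test shows a significant rise is

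Φ( g√110 / √[2(1 − ρ)] − 1.96 ).

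For g = 0.2 and ρ = 0.5 this is Φ(2.098 − 1.96) = 0.555.

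A simulation of 20,000 trials per row, using the exact t tests, gave:

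| g (SD) | ρ | Formula | Simulated: trained-arm paired test, significant rise | Simulated: between-arm t test at T1 |
|---|---|---|---|---|
| 0 | 0.5 | – | 2.6% | 4.9% |
| 0 | 0.7 | – | 2.3% | 5.0% |
| 0.1 | 0.5 | 18.1% | 18.5% | 5.3% |
| 0.1 | 0.7 | 27.2% | 27.1% | 5.0% |
| 0.2 | 0.5 | 55.5% | 54.9% | 5.0% |
| 0.2 | 0.7 | 77.3% | 76.4% | 5.0% |
| 0.3 | 0.5 | 88.2% | 87.3% | 5.2% |
| 0.3 | 0.7 | 98.2% | 98.2% | 4.8% |

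The paired column counts improvement only, so its nominal value with no gain is 2.5%. The between-arm column counts both directions, so its nominal value is 5%. An equal gain in both arms cancels from the between-arm difference.

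**3. Does naming the between-arm test strain the sample size?** With 110 per arm, two-sided 5% and 80% power, the detectable difference is (1.960 + 0.842) × √(2/110) = 0.38 SD. On the protocol's own 10% against 1%, a two-sided 5% comparison of proportions has about 84% power. No change in sample size follows from this point.

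**4. Mean item score against total score.** The questionnaire has 30 + 6 × 5 = 60 items and a maximum of 60. If each item scores one point and all are answered, the mean item score is the total divided by 60. Dividing every score by a constant leaves the t statistic and P value unchanged.

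**The case against.** The strongest reply is that the comparison that matters is already in the plan. A between-arm t test is planned directly after the paired tests, under intention to treat. The objective is framed against the waitlist, the sample size contrasts two arms, and the Primary outcome section fixes literacy immediately post intervention. This stands. A reader might infer that effectiveness is to be judged by paired tests alone, or by a rule that the trained arm is significant and the control arm is not. The document states neither, so no error rate is given here for such a rule.

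The Study design sentence can also be read as a measurement schedule within a randomized trial. That reading is fair. The sentence nevertheless links effectiveness to pre-post measurement, and nothing later says that the paired tests are only supportive.

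On Table 2, the footnote may simply mark the instrument wherever it appears, and the Primary outcome text settles the time. So it would be too strong to say that several scores and times compete for the primary claim. What remains is a table that does not match the text. The wording about knowledge and attitudes scores most naturally refers to the same questionnaire, which Table 2 names in similar terms.

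Finally, an article may leave the ranking of analyses to a fuller document. The point does not rest on that omission alone. It rests on what is printed: paired tests given equal standing and described wrongly, a between-arm test with no target, and a footnote at odds with the text.

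**Conclusion.** The point holds as a badly fixed analysis, not as a missing comparison. The plan contains the right kind of test but does not make it decisive, and sets beside it, at the same significance level, tests that cannot tell training from retesting.

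If a trained-arm paired test were read as evidence of effect, a retest gain of 0.1 to 0.3 SD with no training effect would produce a significant rise in about 19% to 98% of trials, against about 5% for the between-arm test at T1. The range depends on the assumed gain and on the assumed correlation of 0.5 to 0.7, neither of which the document supplies. The direction does not depend on them: any gain common to both arms inflates the paired test and cancels from the between-arm test.

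The difference between mean item score and total score is only one of labelling, under the conditions in step 4 of the working.

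**What to change.** - In **Statistical analysis**, state that the primary test is the between-arm difference in the 0-60 literacy total at T1, by allocated arm, two-sided 5%, and that T2 and all other scores are secondary.
- Report within-arm changes descriptively with confidence intervals, say that they are not evidence of effectiveness, and correct the description of paired tests so that it refers to change within teachers.
- Use the 0-60 total as the name of the primary score throughout.
- In **Study design**, make clear that the pre and post measurements are the assessment schedule and that effectiveness is judged between arms.
- In **Table 2**, keep the primary-outcome footnote in the immediate post-intervention column only.

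The cost is a few sentences and one table footnote. No extra data are needed and the sample size stays as it is.

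### The primary between-arm test leaves out the baseline literacy score, so it is valid but less precise than the planned data allow

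*Protocol article*

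**What the plan says.** The Primary outcome section sets the endpoint and its time: "The primary outcome measures for the trial is teachers’ mental health literacy immediately post intervention". It is scored as a number: "A total score out of 60 maximum will be calculated".

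The Study design section plans the measure at all three time points: "Participants’ mental health literacy and self-efficacy will be evaluated using questionnaires pre and post training and at 3 months’ follow-up". Forms are anonymous and carry a self-chosen identifier. Of that identifier, the Procedure for informed consent section says: "This information will be used to link pre-and post-training responses".

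Statistical analysis then names two kinds of test for teachers' scores. Across time points, paired-samples *t* "tests will be used to examine differences in knowledge and attitudes scores and self-efficacy between participants at T0, T1 and T2". Between arms, "Differences in mean scores between the study and control groups will be evaluated using an independent samples" *t* test. The article contains no covariate, change score or regression model for the comparison of arms. The choice of test is therefore stated outright and is not a detail left for another document.

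**The concern.** The baseline score is collected on the same scale as the outcome and is meant to be linked to it, yet the comparison that answers the primary question does not use it. The paired tests do not fill the gap. They describe change over time and give no estimate of the difference between arms.

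If T0 and T1 scores are correlated within arms, part of the spread in T1 scores is predictable before training starts. An unadjusted test counts that part as noise. The result is a wider interval and a lower chance of detecting a real effect from the same teachers and questionnaires. The sample size statement gives no power for a comparison of mean scores, so the plan offers no assurance that this precision can be spared.

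**Working it through.** **The plan's own figure.** Participants and sample size gives 110 per arm from a 90% confidence interval, 5% absolute precision, and improvement of 10% versus 1%. The precision formula for a difference of two proportions is n = z² [p₁(1−p₁) + p₂(1−p₂)] / d². With z = 1.645, p₁ = 0.10, p₂ = 0.01 and d = 0.05, n = 2.7055 × (0.0900 + 0.0099) / 0.0025 = 108.1. That rounds up to 109 per arm, in line with the stated 110. The calculation concerns percentages and does not rest on the t test, so this point does not make it wrong.

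**Inputs.** 110 per arm (Participants and sample size) and significance level 0.05 (Statistical analysis), taken as two-sided because the article does not say. The within-arm T0–T1 correlation r is not in the article. It is assumed and shown as a range.

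**Unadjusted t test.** The difference detectable with 80% power, in SD units, is (1.960 + 0.842) × √(2/110) = 2.802 × 0.1348 = 0.378.

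**Adjusted for T0.** The variance of the arm difference is multiplied by 1 − r², so the detectable difference is 0.378 × √(1 − r²). The equivalent unadjusted sample is 110 / (1 − r²) per arm.

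| Assumed r | Variance cut (r²) | Detectable difference (SD) | Power at 0.378 SD | Equivalent n per arm |
|---|---|---|---|---|
| none (t test) | 0% | 0.378 | 80% | 110 |
| 0.3 | 9% | 0.360 | 83.6% | 121 |
| 0.5 | 25% | 0.327 | 89.9% | 147 |
| 0.6 | 36% | 0.302 | 93.8% | 172 |
| 0.7 | 49% | 0.270 | 97.5% | 216 |

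**Simulation check.** 220 teachers in 6 schools, individual unstratified randomisation, 2,500 runs per setting; r and the school intraclass correlation (ICC) are assumed.

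- With no true effect, the t test rejected in 4.6% to 5.5% of runs across the five settings. It holds its nominal level.
- At 0.378 SD, r = 0.5 and ICC 0.05, power was 80.4% for the t test, 90.8% for ANCOVA on T0, and 91.0% with school added.
- At r = 0 and ICC 0, power was 80.3% for the t test, 80.1% for ANCOVA on T0, and 78.9% with school added. A useless baseline covariate costs almost nothing.

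**Linkage.** If a fraction f of teachers had no linkable T0 form and were dropped, the variance factor would be (1 − r²) / (1 − f). This equals 1 when f = r². A loss of 9% of teachers would cancel the gain at r = 0.3, and a loss of 25% would cancel it at r = 0.5. Unlinked teachers therefore need to be kept.

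**The case against.** **This is efficiency, not error.** That stands. A reader might infer that chance imbalance at baseline biases the planned comparison. It does not: under individual randomisation the t test is unbiased, and its standard error already allows for chance imbalance. Nothing in the Statistical analysis section is false or contradictory on this point.

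**Intention to treat.** A reader might also infer that t tests are complete-case and so conflict with "Intention-to-treat analysis will be used for data analysis". The article does not support this. It states no missing-data rule, such a rule is commonly left to a fuller document, and comparing teachers as allocated with a t test is compatible with intention to treat. An ANCOVA of T1 would also leave out teachers with no T1 score unless a rule were added.

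**Baseline may not be usable for everyone.** This stands in part. Linkage depends on an anonymous item such as the mother's first name, so mismatches are foreseeable, and it would be wrong to say that baseline is known for every teacher. A T1 comparison needs the arm label but not necessarily an individual T0 link. However, the planned paired tests already need the link, and unlinked teachers can be kept by a simple rule.

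**School.** It is tempting to add that ignoring school loses precision. The figures do not bear this out: adding school moved power only from 90.8% to 91.0%, and the Study setting section describes schools chosen to be broadly alike.

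**The size is assumed.** This stands. The article gives no SD, no correlation and no target difference in SD units, so the low end, r = 0.3, has to be shown with the rest.

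**Could a change score be meant?** The text says mean scores. Even so, a change-score test has variance factor 2(1 − r): 1.4, 1.0, 0.8 and 0.6 for r = 0.3, 0.5, 0.6 and 0.7. ANCOVA gives 0.91, 0.75, 0.64 and 0.51, lower in every case.

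**Conclusion.** The point holds as a loss of efficiency in the primary comparison. The article fixes a valid but unadjusted test when a baseline measure of the same outcome is already planned. The gain from using it is modest at r = 0.3 and substantial at r = 0.5 or above. Its true size cannot be settled from the article. The figures rest on the assumed correlations, 110 analysed teachers per arm, a two-sided 5% level, and unlinked teachers being kept. The stated sample size is not undermined. The change is advisable but is not a condition for the trial's validity.

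**What to change.** State the primary analysis as an ANCOVA of "mental health literacy immediately post intervention" (T1 total score) on allocated arm, with the T0 total score as covariate. Report the adjusted difference with its 95% CI. Keep the unadjusted t test as a sensitivity analysis.

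Add a rule that keeps teachers whose T0 form cannot be linked, for example the overall T0 mean together with a missing-baseline indicator, so that adjustment does not shrink the sample. School may be entered as a fixed effect, but little gain should be claimed for it.

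The cost is one paragraph of analysis wording. ANCOVA is available in the named software, and no new data or visits are needed. As the trial is already under way, the change should be dated and made before outcome data are examined by arm.

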### Intervention

The intervention group will receive a training workshop based on a local adaptation of the WHO-EMRO School Mental Health Manual. The training was adapted in light of in-depth interviews by teachers and school administrators and discussions with relevant stakeholders to make it suitable for the Pakistani school system. The training will be three 6-h sessions delivered face-to-face over a 2-week period. Teachers can decline to participate or withdraw at any stage. Topics to be covered in training workshop are given in Table 1.

**Table 1 Tab1:** Summary of the modules in the World Health Organization, Eastern Mediterranean Region (WHO-EMRO) School Mental Health Manual

Module	Description
Module 1. Social-Emotional Childhood Development	• Developmental tasks of primary-school-age children (6–12 years) • Developmental tasks of secondary-school-age children (12–18 years) • Moral development • Brain development and implications for schooling
Module 2. Mental Health Promoting Schools (Promotion and Prevention)	• Core values of a mental health promoting school • The role of parents in their children’s education • Behavioral management strategies for schools Discipline and management of disruptive behavior Counseling Circle time • Physical health promoting efforts that impact mental health Nutrition Vision/ hearing/ speech Physical exercise • Media and mental health Screen time Internet addiction Cyberbullying • Suicide prevention
Module 3. Addressing Student Mental Health Problems in Your Classroom (and when to refer for additional help)	• Recognizing warning signs for different disorders: Depression Anxiety Pervasive developmental disorders Attention disorders Psychotic disorders Specific learning disorders Intellectual disability Conduct disorders Substance abuse • When to refer to a specialist for evaluation and treatment

The workshop will be conducted by the principal investigator (PI) along with one to two assistants (psychologists trained by the PI). The PI was trained over a period of 2 days by one of the WHO trainers and a Master Trainer of school mental health. ([name]). Participants will be provided with standardized school mental health manual handouts.

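### The analysis is labelled intention-to-treat, but the only between-arm test named uses only teachers with a score at T1 and ignores T0, so selective loss before T1 could bias the primary comparison

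*Protocol article*

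**What the plan says.** The primary endpoint is fixed at T1: "The primary outcome measures for the trial is teachers’ mental health literacy immediately post intervention" (Primary outcome section). Table 2 shows that the same literacy questionnaire is also given at baseline (T0) and at 3 months (T2).

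The Statistical analysis section names two tests for teacher scores. Paired *t* "tests will be used to examine differences in knowledge and attitudes scores and self-efficacy between participants at T0, T1 and T2". The comparison of arms reads "Differences in mean scores between the study and control groups will be evaluated using an independent samples" *t* test. The section then states "Intention-to-treat analysis will be used for data analysis". The only mention of losses concerns reporting: "Data on screening, refusals and dropouts will be reported as per Consolidated Standards of Reporting trials (CONSORT) guidelines".

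The Intervention section gives the trained arm three sessions of six hours each within two weeks and adds "Teachers can decline to participate or withdraw at any stage". Under Study design, the waitlist arm receives no training during the study.

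**The concern.** Intention-to-treat has two parts: teachers are compared in the arm to which they were randomised, and all randomised teachers count. The named test meets the first part. It cannot meet the second once T1 forms are missing, because a teacher with no T1 score contributes nothing, even though the T0 score is in hand.

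The two arms face different demands before T1. One has 3 × 6 = 18 hours of attendance, the other has none, and T1 falls directly after the course. Leaving the course and missing the primary form could therefore coincide, in one arm only. If the teachers lost were those with lower scores, the trained teachers who remain would look better at T1 without any training effect. The Dissemination section says an effective result will go to policy-makers with a view to mandatory teacher training, so a difference produced by who stayed would matter.

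**Working it through.** **1. Who enters each analysis.** The independent-samples *t* test uses observed T1 scores only. The paired test needs both forms of a pair. A model for T0, T1 and T2 together keeps a teacher who has T0 but no T1.

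**2. Is there an allowance for loss?** Participants and sample size states 110 per arm, from a 90% confidence interval, 5% absolute precision, and 10% against 1% improvement. The precision formula reproduces it:

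n = 1.645² × [0.10 × 0.90 + 0.01 × 0.99] / 0.05² = 2.706 × 0.0999 / 0.0025 = 108.1, so 109 per arm.

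The stated 110 leaves one spare teacher per arm (1/110 = 0.9%). The sample size therefore gives no dropout rate, stated or implied, that could be used below.

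**3. Bias by formula.** Assume no true effect, loss of a fraction d in the trained arm only, and correlation r between the tendency to stay and the T1 score. With z the normal quantile for d and φ the normal density:

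bias (in SD) = r × φ(z) / (1 − d).

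For d = 0.20, φ(−0.842) / 0.80 = 0.280 / 0.80 = 0.35. With r = 0.3 the bias is 0.105 SD, and with r = 0.5 it is 0.175 SD. The standard errors are 0.142 and 0.139, so the two-sided 5% test rejects in about 11.5% and 24% of trials. Simulation with 20,000 runs gave 11.2% and 23.7%. For d = 0.05 the bias is 0.02 to 0.05 SD for r = 0.2 to 0.5, and the false-positive rate is 5% to 7%.

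**4. Simulation with a different mechanism.** Assumptions: 110 per arm, no true effect, T0–T1 correlation 0.6, and 5% of controls missing at random. Loss in the trained arm follows a logistic model with 2.7-fold odds per SD lower score (steep) or 1.65-fold (weaker). False-positive rates of the independent *t* test:

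| Trained-arm loss | Steep, depends on T0 | Steep, depends on T1 | Weaker, depends on T0 | Weaker, depends on T1 |
|---|---|---|---|---|
| 5% | about 6% | 6–7% | 5% | 5–6% |
| 10% | about 7% | 9–10% | 5–6% | 6–7% |
| 20% | about 12% | about 23% | 6–7% | 10% |

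Repeat runs differ by about one percentage point; for example, the steep T0-dependent case at 20% loss gave 11% to 12%. At 20% loss with steep dependence, the *t*-test bias is about 0.10 SD (T0-dependent) and 0.17 SD (T1-dependent).

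**5. What using T0 achieves.** When loss depends on T0, a T0-adjusted model has no bias and holds about 5% at every loss rate. When it depends on the unseen T1 score, the model helps but does not cure: at 20% loss with steep dependence, about 0.11 SD of bias and a false-positive rate of 16–17% remain. A sensitivity analysis is therefore needed as well.

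**The case against.** The strongest case against is that this is a condensed article. A *t* test is compatible with intention-to-treat in the sense of comparing teachers as randomised, and missing scores might be imputed first. A full protocol or analysis plan, not shown, could contain such a rule and could arrange measurement of teachers who stop the course. That stands to this extent: the absence of a missing-data section is not the point here. What remains is that the article fixes a between-arm test that ignores T0 and, as written, cannot include a teacher without T1, under a label that suggests everyone is included.

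A reader might infer more: that the plan is a completers' analysis, that the training effect will be biased upwards, or that the 5% error rate is already lost. The documents do not support any of these.

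- They never say that only completers are analysed.
- Stopping the course is not the same as failing to return the T1 form, and the article does not link the two.
- T1 follows a two-week course, and teachers expecting to leave the school within 3 months are excluded, so there is little time for loss.
- Waitlist teachers, who receive nothing during the study, may also fail to return forms, which could shrink or reverse the imbalance.
- No dropout rate, correlation or mechanism is given. At 5% loss the effect is small.

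**Conclusion.** The point holds as a mismatch between the intention-to-treat label and the named primary test, with a risk of bias that is plausible but cannot be sized from the documents. Under steep dependence of loss on score, the false-positive rate would be about 6–7%, 7–10% and 12–23% at 5%, 10% and 20% trained-arm loss. Under weaker dependence it would be about 5–6%, 5–7% and 6–10%. These figures rest on assumed loss rates, an assumed T0–T1 correlation of 0.6, 5% random loss among controls, and lower scorers being the ones lost. If others are lost, the bias could be absent or run the other way. The change is worth making because a clearly better analysis is available from data already planned, and it protects fully when loss depends on T0 and partly when it depends on T1.

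**What to change.** 1. In the Intervention and Statistical analysis sections, state that a teacher who stops the training is still offered the T1 and T2 forms, unless consent is withdrawn.
2. Replace the independent *t* test as the primary analysis with a baseline-using model for all randomised teachers. One choice is a likelihood-based mixed model on T0, T1 and T2 (arm by time, common baseline mean), with the result read at T1. Analysis of covariance with multiple imputation would serve equally.
3. Report T1 return by arm, and add a delta-adjusted (tipping-point) analysis: lower the imputed trained-arm T1 scores step by step and show how large the shift must be before the conclusion changes.

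Filling missing trained-arm scores from the control distribution would not be enough, because the selected observed scores stay in place. In the case with 20% T1-dependent loss, it leaves 0.80 × 0.175 = 0.14 SD of bias and a false-positive rate of about 15–16%.

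The cost is rewording and a few hours of analysis. Mixed models are available in the stated software, and linking of forms is already planned. The downside is possibly a less favourable sensitivity estimate. No extra teachers or assessment times are needed.
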